## Abstract

**Background:**

Self-monitoring of glucose is an essential component of type 1 diabetes (T1D) management. In recent years, continuous glucose monitoring (CGM) has provided an alternative to daily fingerstick testing for the optimisation of insulin dosing and general glucose management in people with T1D. While studies have been conducted to evaluate the impact of CGM on clinical outcomes in the US, Europe and Australia, there are limited data available for low- and middle-income countries (LMICs) and further empirical evidence is needed to inform policy decision around their use in these countries.

**Methods:**

This trial was designed as a pragmatic, parallel-group, open-label, multicentre, three-arm, randomised (1:1:1) controlled trial of continuous or periodic CGM device use versus standard of care in people with T1D in South Africa and Kenya. The primary objective of this trial will be to assess the impact of continuous or periodic CGM device use on glycaemic control as measured by change from baseline glycosylated haemoglobin (HbA1c). Additional assessments will include clinical outcomes (glucose variation, time in/below/above range), safety (adverse events, hospitalisations), quality of life (EQ-5D, T1D distress score, Glucose Monitoring Satisfaction Survey for T1D), and health economic measures (incremental cost-effectiveness ratios, quality adjusted life years).

**Discussion:**

This trial aims to address the substantial evidence gap on the impact of CGM device use on clinical outcomes in LMICs, specifically South Africa and Kenya. The trial results will provide evidence to inform policy and treatment decisions in these countries.

**Trial registration:**

NCT05944731 (Kenya), July 6, 2023; NCT05944718 (South Africa), July 13, 2023.

## Introduction

### Background and rationale {6a}

Self-monitoring of glucose via regular daily fingerstick glucose testing is an essential component of managing people with type 1 diabetes (T1D) [1]. However, in recent years the development of continuous glucose monitoring (CGM) devices has provided an alternative option for optimising insulin dosing and glycaemic control in people with T1D [2]. A systematic review of the use of real-time CGM and intermittent CGM showed that CGM was associated with a reduction in glycated haemoglobin (HbA1c; weighted mean difference: -0.17% [95% confidence interval {CI} -0.29, -0.06]), and an increase in the time users spent with daily glucose levels ‘in-range’ (usually 70–180 mg/dL; weighted mean difference: + 70.7 min [95% CI +46.7, +94.8]) [1]. Of the two CGM schedules assessed, real-time CGM use was shown to provide the greatest reduction in HbA1c (weighted mean difference: -0.23% [95% CI -0.36, -0.10]) and the greatest increase to the time ‘in-range’ (weighted mean difference: +83.5 min [95% CI +52.7, +114.3]) [1]. These findings have also been supported by the results of several individual studies, where CGM was found to improve glycaemic control in people with T1D and reduce the frequency of hypoglycaemic events [2–4].

However, this body of evidence consists primarily of studies conducted in the United States (US) [1, 3, 4], Europe [1, 2], or Australia [1], and there are limited data on the effects of CGM on clinical outcomes in low- and middle-income countries (LMICs), where CGM devices may not be readily available. A recent scoping review of CGM in LMICs did not identify any randomised trial conducted in Sub-Saharan Africa [5], and to our knowledge only one study on the use of CGM in people with T1D has been conducted in the region, which was a feasibility study in Kenya and Uganda and not a randomised control trial [6]. Similarly, we have identified no randomised trials conducted in South Africa that have evaluated the impact of CGM compared with standard of care glucose monitoring on HbA1c (and other clinical outcomes) in people with T1D, with the majority of the evidence base consisting of qualitative, mixed methods, and perception studies [7–10]. Overall, there exists a substantial evidence gap on the use of CGM in people with T1D in LMICs, particularly those in Sub-Saharan and Southern Africa, and while some devices have received US Food and Drug Administration (FDA) approvals or European Commission “Conformité Européenne” CE marks [11], further empiric evidence is needed to inform policy decision around their use in these countries as evidence generated in higher resource settings may not be applicable [11–13].

The rationale for selecting Kenya and South Africa as study locations is rooted in different reasons. In South Africa, 31,500 people live with T1D, with an annual growth rate of 6.1% [14]. In Kenya, there are 23,100 people living with T1D, with an annual growth rate of 4.2% [15]. There are different levels of care provision for T1D in both countries, which translates into different approaches to T1D management. Additionally, there are different levels of CGM availability in both countries.

Here we present the protocol for a pragmatic trial that aims to assess the impact of continuous or periodic CGM device use on glycaemic control (and other clinical, quality of life, and health economic outcomes) in people with T1D in South Africa and Kenya. The trial was co-designed by diabetes stakeholders in South Africa and Kenya and are sponsored by FIND. The trial was designed to incorporate CGM use within the routine care in diabetes clinics in multiple centres, necessitating slight variations in design for each centre as routine care differed. The trial has been designed in accordance with the principles of the Declaration of Helsinki and country-specific regulatory and ethics requirements and has been approved by all relevant Institutional Review Boards (IRBs) and Independent Ethics Committees (IECs).

### Objectives {7}

The overall objective of this trial is to assess the impact of CGM (Intervention) on glucose levels (Outcome) compared with standard of care (Comparator) in people with T1D in South Africa and Kenya (Population).

#### Objectives

The primary objective is to evaluate the impact of continuous and periodic CGM on changes to HbA1c levels in people with T1D in South Africa and Kenya, compared with standard of care.

Secondary objectives are as follows (versus standard of care where appropriate):To evaluate the impact of continuous or periodic CGM device use on glucose variability.To evaluate the impact of continuous or periodic CGM device use on the number of unplanned visits to outpatient clinics and/or hospitals as a result of diabetes complications.To evaluate the acceptability and feasibility of continuous or periodic CGM device use from the perspective of the participant, caregiver, and healthcare provider.To evaluate the cost of continuous or periodic CGM device use from a user and provider perspective.

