#### Secondary outcomes

Unless otherwise stated, the secondary outcomes listed below will be presented using descriptive statistics (i.e., means, standard deviations) or as intervention effects with 95% CI.CGM device outputs: (i) Coefficient of variation (%CV) for glucose levels; (ii–iv) the time spent ‘in-range’, below-range’, and ‘above range’ (percentage per day and absolute values [hours/minutes]).Number of hospitalisations due to diabetes complications.Health-related quality of life (HRQoL): (i) mean change from baseline in EQ-5D-Y/EQ-5D/EQ-5D-interviewer-administration scores [18–20]; (ii) mean change from baseline in type 1 diabetes distress (T1D-DDS) scores for participant and parent (where possible) [21]; (iii) qualitative assessment using focus group discussions with participants and caregivers.Adherence to CGM device use: the proportion of scheduled time registered using the CGM device (automatic device output).Acceptability: (i) mean change from baseline in Glucose Monitoring Satisfaction Survey for T1D (GMSS-T1D) score; [22] (ii) qualitative assessment using semi-structured interviews with healthcare providers and focus group discussions with participants.Cost: surveys will capture both direct and indirect costs of diabetes care at follow-up Visits 3 to 6 for trial participants, their caregivers (if possible), and healthcare providers. Incremental cost-effectiveness ratios (ICERs) and quality adjusted life years (QALYs) will be used for between-group comparisons.

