**ASSESSMENTS**							
Doctors visit (medical chart review)			All	All	All	All	All
HbA1c assessment		All		All	All	All	All
Medical events and resources survey				All	All	All	All
GMSS		All		All	All	All	All
HRQoL assessments		All		All	All	All	All
DDS		All		All	All	All	All
Acceptability questionnaire				Arms 1 and 2	Arms 1 and 2	Arms 1 and 2	
Focus group discussion^c^						All	

*CGM* Continuous glucose monitoring, *DDS* Diabetes distress score, *GMSS* Glucose Monitoring Satisfaction Survey, *HRQoL* Health Related Quality of Life

^a^Includes identification of potential participants to be invited to the screening and enrolment day

^b^In the continuous CGM arm, the device is applied once on Day 1 and used until Month 9, for the periodic arm, a new device is provided at the visits shown and used for 1 week before each clinic visit (except for the enrolment visit), and for 1 week after each clinic visit (except for the final follow-up visit)

^c^Performed in a subset of participants

**Table 2 Tab2:** Schedule of assessments (South Africa study; NCT05944718)

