## Statistical methods

### Statistical methods for primary and secondary outcomes {20a}

A separate Statistical Analysis Plan will provide a detailed description of the planned statistical analyses and only a brief outline will be presented here. Please see the ‘Outcomes {12}’ section for definitions of the primary, secondary and exploratory outcomes and for further details on data presentation.

For the purposes of this trial, the following populations will be defined:Enrolled population: all participants enrolled in the trial who completed informed consent.Assigned population: all participants who have been assigned to a trial arm and completed all Day 1 trial visit procedures.Fully Complied: all participants who fully complied with the protocol.Partly Complied: all participants who recorded HbA1c values at Visit 1 and 5 (at least).Intervention: all participants in the CGM device arms who fully complied with the protocol.Safety: all participants who have been assigned to a trial arm.

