#### Secondary outcomes

Glucose variation will be assessed using the Intervention population, with %CV calculated as the ratio of the standard deviation to the mean. HRQoL outcomes will be analysed using the Fully Complied or Partly Complied populations and two-way repeated-measures ANOVA with time and arm as independent variables. Within-group mean GMSS scores will be analysed using t-tests and between-group scores using repeated-measures two-way or one-way ANOVA (depending on the availability of data) with time and arm as independent variables (all using the Fully Complied or Partly Complied populations).

All other secondary outcomes will be analysed using descriptive statistics: hospitalisations using the Partly Complied population, adherence using the Intervention population, and cost surveys using the Fully Complied or Partly Complied population.

For the cost analysis, standard bottom-up costing methods from a partial societal perspective will be used to estimate the costs of both direct and indirect resources utilised by participants over the trial period. Unit costs will be assigned to these resource outputs using values sourced from public sources: laboratory test costs from the relevant national laboratory service, staffing costs from the Salaries and Renumeration Commission, medicine and supply costs from Kenya Medical Supplies Authority (KEMSA)/Mission for Essential Drugs (MEDs), minimum wage data from the relevant government agency, and the cost of procedures and in-patient hospital stays from the National Health Insurance Fund. Where necessary, unit costs will be sourced from other publicly available resources and the literature. ICERs will be calculated using the primary outcome measure and the time ‘in-range’, and QALYs will be calculated from the HRQoL outcomes.

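### Secondary objective 2 concerns unplanned outpatient and hospital visits, but the only matching outcome is hospitalisations, and these are only described by arm

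*Protocol article*

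**What the plan says.** In the protocol article, Objectives {7} introduces the list with "Secondary objectives are as follows (versus standard of care where appropriate" and gives as its second item the "number of unplanned visits to outpatient clinics and/or hospitals as a result of diabetes complications".

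Outcomes {12}, Secondary outcomes, contains one entry on this subject: "Number of hospitalisations due to diabetes complications". The opening rule of that section is that, unless otherwise stated, secondary outcomes are "presented using descriptive statistics (i.e., means, standard deviations) or as intervention effects with 95% CI".

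Statistical methods {20a} sends the reader back to Outcomes {12} for the outcome definitions. Its Secondary outcomes paragraph then fixes the analysis: "All other secondary outcomes will be analysed using descriptive statistics: hospitalisations using the Partly Complied population". That population is defined as "Partly Complied: all participants who recorded HbA1c values at Visit 1 and 5 (at least".

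Tables 1 and 2 both list a "Medical events and resources survey" for all arms at Months 3, 6, 9 and 15. The article does not show its questions. The cost analysis will "estimate the costs of both direct and indirect resources utilised by participants over the trial period", without naming outpatient visits.

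**The concern.** An objective needs an outcome that measures what it names. Here the objective names unplanned contacts with outpatient clinics or hospitals, and the outcome counts admissions. The analysis section then offers no between-arm estimate, although the objective is about impact and all three arms can have these events.

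Followed as written, the trial would not report unplanned outpatient use by arm as an outcome. A table of admissions could be taken as the answer to the whole objective, in a trial meant to inform policy. If visit counts appeared later, in an open-label trial, a reader of this article could not tell whether they had been planned.

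**Working it through.** The check is mainly a comparison of texts.

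**1. What each definition counts.** Split the events due to diabetes complications into four kinds:

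- U: unplanned outpatient visits
- V: unplanned hospital visits without admission
- A: unplanned admissions
- P: planned admissions

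| | U | V | A | P |
|---|---|---|---|---|
| Objective | yes | yes | yes | no |
| Listed outcome | no | no | yes | not excluded |

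The objective counts U + V + A. The outcome counts A + P. They share only A, so the outcome is narrower in two respects and wider in one. It is not strictly a subset of what the objective names.

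**2. What analysis is fixed.** Outcomes {12} allows either description or an intervention effect with 95% CI, unless otherwise stated. Statistical methods {20a} names hospitalisations and states description. Read together, the specific statement governs and no between-arm estimate is fixed.

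**3. Whether another outcome fills the gap.** The remaining secondary outcomes are CGM outputs, quality of life, adherence, acceptability and cost. None is a count of visits. Visits may enter the cost analysis, but as cost.

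**4. Figures.** The article gives no figure on this point. Its sample size of 246 is for HbA1c. It reproduces as a one-way ANOVA with three arms, effect size f = 0.2 and 5% significance (power 0.804 at 246, 0.798 at 243), but it does not bear on visits.

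The precision of an estimate can only be illustrated. Assume 82 per arm, 15 months for everyone, no dropout and Poisson counts. Person-years per arm are 82 × 1.25 = 102.5. For a true rate ratio of 1, SE(log rate ratio) = √(2 / events per arm), and the 95% limits are exp(±1.96 × SE).

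| Assumed rate per person-year | Events per arm | 95% limits |
|---|---|---|
| 0.1 | 10.25 | 0.42 to 2.38 |
| 0.2 | 20.5 | 0.54 to 1.84 |
| 0.4 | 41 | 0.65 to 1.54 |
| 0.5 | 51.25 | 0.68 to 1.47 |

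Overdispersion or dropout would widen all of these.

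A formal test would usually be weak. With 82 per arm and assumed proportions hospitalised, power is 0.23 (10% v 5%), 0.43 (20% v 10%), 0.31 (30% v 20%) and 0.80 (40% v 20%). This supports estimation with an interval and not a powered comparison.

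**The case against.** The strongest reply has four parts.

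- **The objective is partly met.** Admissions are counted in a randomised trial with a standard-of-care arm, so counts by arm do inform the hospital part. The comparison is also qualified by the words on appropriateness. This stands. A reader might infer that the objective cannot be answered at all, and the documents do not support that.
- **Describing a secondary outcome is legitimate.** This stands too, especially if events are few, and the article calls its statistical section a brief outline with detail left to a separate plan. But the article does fix description for this outcome by name, and a statistical analysis plan does not normally supply an outcome that the protocol's own list lacks. Low power argues against a test, not against an estimate with its interval.
- **The survey may already record visits.** It may. Its content is not shown, so neither its adequacy nor a loss to the cost objective can be asserted.
- **The size is assumed.** A reader might infer that the outcome is a rarer subset of the intended events and that precision suffers by a known amount. Neither follows: planned admissions are not excluded, and every rate in the table is an assumption.

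What remains is the mismatch between the stated objective and the stated outcome, which none of these points removes.

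**Conclusion.** The concern holds in a limited form. The outpatient and non-admission part of secondary objective 2 has no defined outcome or analysis. The hospital part is covered by an outcome that does not exclude planned admissions and is described by arm without a fixed between-arm estimate. The conclusion rests on the wording of the objectives, outcomes and statistical sections alone, and no assumed rate is needed for it.

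It touches one of four secondary objectives and leaves the primary analysis unaffected. It should be corrected because the passages disagree and the remedy is cheap.

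**What to change.** **Preferred change.** In Outcomes {12}, define the outcome as the number of unplanned outpatient and hospital visits for diabetes complications, with hospitalisations as a component. Take it from the medical events survey at Months 3, 6, 9 and 15, if that survey records such visits. In Statistical methods {20a}, replace description alone with event rates by arm and a between-arm estimate with 95% CI for each CGM arm against standard of care. A rate ratio allowing for overdispersion, such as a negative binomial model, is one option among several. Label it as estimation, not a powered test.

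**Alternative.** If the survey does not capture unplanned visits, narrow the objective to hospitalisations and state that outpatient use is not assessed as an outcome.

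**A related point on the population.** The Partly Complied set requires an HbA1c value at Visit 5, so people who leave before Month 9 drop out of the count. An estimate made in that set is not a comparison of everyone randomised, and the text should say so.

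**Cost.** An amendment to the wording with ethics submission, and a small extra analysis. Intervals will be wide if events are few. No new visit or procedure is needed. South African recruitment began in September 2023 and January 2024, so any survey item added after that would miss earlier visits.

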### Trial design {8}

This trial is a pragmatic, parallel-group, open-label, multicentre, three-arm, superiority randomised (1:1:1) controlled trials of continuous or periodic CGM device use (the Abbott Freestyle Libre 1 device) versus standard of care in people with T1D in Kenya and South Africa. The primary endpoint is the mean change in HbA1c levels. The trial was designed using the PRECIS-2 tool, a nine-domain tool intended to be used in the trial design phase, which is intended to align design decisions with applicability of trial results [16]. 

The trial is expected to take approximately 18 months to complete (September 2023 to April 2025 in South Africa, and February 2024 to July 2025 in Kenya), including trial set-up, recruitment, and follow-up for all participants.

## Methods: Participants, interventions, and outcomes

### Study setting {9}

The trial in Kenya will be conducted at three public sector clinics that are part of the ‘Changing Diabetes in Children’ program: the Kenya Diabetes Management and Information Centre, and the Machakos and Kiambu level five referral hospitals. This program was launched in 2012 to improve T1D care in children and young adults (under the age of 18), by working with the Kenyan Ministry of Health to build capacity and strengthen the local health system through the provision of medical equipment, point-of-care glucose meters, healthcare training, and dissemination of best practice methods [17].

The trial in South Africa will be conducted at three public sector clinics: the diabetes clinic at Groote Schuur Hospital in Cape Town; the paediatric diabetes clinic at Red Cross War Memorial Children’s Hospital in Cape Town; and the adult and paediatric diabetes clinic at Steve Biko Academic Hospital in Pretoria.

### Eligibility criteria {10}

#### Inclusion criteria

Participants meeting all of the following criteria will be eligible for enrolment in the trials:People with T1D attending one of the clinics for regular diabetes care, with a current (within the past 3 months in South Africa and 18 months in Kenya) HbA1c level of ≥10%/86 mmol/mol and no record of an HbA1c < 8%/ <64 mmol/mol within the past 9 months.oCaregivers of children or adolescents with T1D will be eligible for inclusion in the trial (for acceptability and feasibility assessments) only if the child or adolescent is also enrolled in the trial.oHealthcare providers will be eligible for inclusion in the trial (for acceptability and feasibility assessments) only if they are engaged in trial-related diabetes care at one of the trial clinics (trial Investigators are excluded).

#### Exclusion criteria

Participants will be excluded from the trial if they meet any of the following criteria:People with T1D under 4 years old, as per the trial CGM device (Abbott Freestyle Libre) manufacturer’s instructions for minimum age of use.People diagnosed with T1D within the past 2 years.People who have used a CGM device within 18 months (in Kenya) and 6 months (in South Africa) of trial enrolment.People who anticipate they would have access to a CGM device through means outside of the trial, during the duration of the trial (15 months).People with type 2 diabetes.People with known pregnancy at the time of trial enrolment.People who are not willing to agree to the CGM device (Abbott Freestyle Libre) terms and conditions.

### Who will take informed consent? {26a}

The trial Investigator or his/her representative will explain the nature of the trial to all participants who meet the inclusion criteria (or their legally authorised representative) and answer all questions they may have about the trial. After being informed that their participation is voluntary and being given ample time to decide whether they wish to take part in the trial, any participants (or their legally authorised representative) who do wish to enrol will be required to sign and date a statement of informed consent that meets the requirements of local regulations and relevant IRB/IECs. For children and adolescents aged 7–17 years (inclusive), they will also be required to sign and date a statement of informed assent that meets the requirements of local regulations and the relevant IRB/IEC. All written informed consent and informed assent must be obtained before the participant is enrolled and any trial-related procedures are performed.

